**3.3.2 Secondary endpoints**

3.3.2.1 Validation of the French version of the VES-13 screening tool

We will use the same validation criteria than for the G8 tool (see previous section): sensitivity, specificity, Youden’s index, predictive values, diagnostic likelihood ratios.

3.3.2.2 Assessment of G8 and VES-13’s intrinsic qualities

We will assess the accuracy and the validity of each screening tool, G8 and VES-13 (Falissard 2001).

**Accuracy assessment:**

**The internal consistency** of each questionnaire will be assessed from answers to every item and according to Cronbach’s alpha coefficient,

The reproducibility will be assessed

- Inter-judges mistakes for G8: comparing the questionnaire filled by the oncologist and the same questions for G8 filled by the nurse (IGE) for each item and the overall score,

- Test-retest for VES-13: comparing the self-questionnaire filled by the patient during the oncology consultation to the questionnaire filled during the geriatrics consultation. This study will be conducted in three centres only: Bordeaux, Lille, and Lyons (60 patients per centre. See chapter 16.1.2 for a justification of the number of patients).

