| **Course of the study** | **Oncological assessment consultation** *(oncologist and nurse)*   - Information leaflet and informed consent, - Assessment of eligibility criteria, - Standard clinical examination (oncologist), - G8 questionnaire (oncologist), - VES-13 self-questionnaire (nurse), - Organisation of appointments for oncological assessment (pre-therapeutic evaluation, extended assessment), and geriatric oncologic assessment.   **Oncological assessment**  The oncological assessment is the extended and standard pre-therapeutic assessments usually performed for patients. Clinical and paraclinical data will be collected for the study.  **Geriatric oncologic assessment** *(geriatrician and geriatric assessment nurse for UPCOG)*  Before starting the oncological treatment and before setting up specific management, within two weeks at least after the oncological assessment consultation.  The nurse (IEG) will have to:   - Filling ADL, IADL, MNA questionnaires, along with the socio-cultural assessment score, - Performing the MMS and Timed Get up and Go tests, - Filling GDS-15 and QLQ- C30 self-questionnaires.   The geriatrician will then receive the patient for an oncological geriatrics consultation and will be in charge of the CIRS-G questionnaire, the synthesis of the self-questionnaires, the oncological geriatrics assessment, and of the clinical file. The doctor will try to recognise the patient for who the setting of a personalised programme of geriatric interventions is required.  **It is essential for the geriatrician not to have access to the G8 nor to the VES-13.**  **Follow-up**  Patients will be followed over 5 years. Data collection will be done at 1 and 5 years in order to collect data on vital status, disease progression, lifestyle (ambulatory, institutionalised). |

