| **Summary of the study course** | **Step 1: Inclusion (J0)**  (Medical oncologists, surgeons, radiotherapists...)  _ Information leaflet  _ Informed consent  _ Inclusion and non-inclusion criteria  _ Inclusion form  **Step 1: Initial oncologic consultation (J0)**  (Medical oncologists, surgeons, radiotherapists...)  _ Booking an appointment for the geriatrics consultation  _ General information on the patient  _ Information on cancer  _ G8 questionnaire  _ VES-13 self-questionnaire  **Step 2: Oncological extended assessment (J0-J30)**  _ Biological data  **Step 3: Geriatrics consultation (J1-J30)**  (Geriatrician and nurse)  _ Geriatric assessment:  _ MMSE  _ ADL, IADL  _ GDS-15  _ QLQ-C30, sociocultural assessment  _ Timed Get up and Go  _ MNA  _ CIRS-G  _ Geriatrician’s recommendations  VES-13 again for 60 patients/centre in three centres:  Bordeaux, Lille and Lyons  **Step 4: Follow-up at 1 and 5 years**  Follow-up data collection (vital status and lifestyle) |

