**3.4.3 Statistical analysis**

The population of the study will be described broadly according to its clinical and sociodemographic characteristics in terms of size and ratio for the qualitative variables and in terms of distribution for the quantitative ones.

Missing data will be reported (by item and by questionnaire) thanks to frequency and percentage. The reasons for these missing data for any test will be described.

The following parameters will be estimated:

- **The sensitivity** will be estimated with the proportion of patients registered as “requiring a geriatric intervention” by the new tool, among the patients having at least one abnormal CGA element. A 95% CI will be reported (binomial distribution).
- **The specificity** will be estimated with the proportion of patients registered as “not requiring a geriatric intervention” by the new tool, among the patients having no abnormal CGA element.

A 95% CI will be reported (binomial distribution).

- **The positive predictive value** will be estimated with the proportion of patients having at least one abnormal CGA element, among the patients registered as “requiring a geriatric intervention” by the new tool. A 95% CI will be reported.
- **The negative predictive value** will be estimated with the proportion of patients having no abnormal CGA element, among the patients registered as “not requiring a geriatric intervention” by the new tool. A 95% CI will be reported (binomial distribution).
- **The ROC curve** representing graphically the sensitivity according to the (1 -specificity) for various thresholds of the assessed test will be represented graphically and help determine the area under the curve (AUC).
- **The internal consistency** will be assessed according to Cronbach’s alpha coefficient (Armitage & Berry, 2002).A 95% CI will be reported.
- **The reproducibility** will be assessed by the intraclass correlation coefficient for quantitative variables, with a 95% CI.
- **Scores between acknowledged subgroups** will be compared thanks to a variance analysis.
- **The area under the ROC curve** for G8 and VES-13 will be compared (Hanley et al, 1983).
- **We will assess whether using both screening tools together** (G8 and VES-13) helps obtaining a more effective screening tool compared to the sole use of one questionnaire (Macaskill et al., 2002).

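### The G8 inter-judge comparison pairs an oncologist's rating at J0 with a nurse's rating at a later visit, so as written it counts real change between visits as rater disagreement

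*Protocol*

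**What the plan says.** The synopsis (Course of the study) gives the first rating to the oncologist, "G8 questionnaire (oncologist"), and the Summary of the study course places it at "Step 1: Initial oncologic consultation (J0").

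For the second rating, section 3.3.2.2 (Accuracy assessment) plans "Inter-judges mistakes for G8: comparing the questionnaire filled by the oncologist and the same questions for G8 filled by the nurse (IGE"), item by item and for the total score. It labels this an inter-judge comparison and gives no day for the nurse's rating. The synopsis introduces the nurse (there abbreviated IEG) as the "geriatric assessment nurse for UPCOG" and lists among her tasks "Filling ADL, IADL, MNA questionnaires, along with the socio-cultural assessment score". The trial rationale says that G8 consists of seven items from the MNA plus age. The MNA appears in the summary under "Step 3: Geriatrics consultation (J1-J30").

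On analysis, section 3.4.3 says that reproducibility "will be assessed by the intraclass correlation coefficient for quantitative variables, with a 95% CI"; the synopsis adds Cohen's kappa for qualitative variables. Neither place limits the interval between the two G8 ratings or breaks agreement down by it. For VES-13, section 3.3.2.2 calls the comparison across these same two visits test-retest.

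**The concern.** An inter-judge coefficient is meant to show how far two raters differ on the same patient in the same state. Here the oncologist always rates first and the nurse always second, on another day. If the patient's nutritional or general state changes in between, that change enters the coefficient as if it were rater error. The label then says something that the data do not show.

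This bears on how the tool will be used. The reproducibility of G8 is a named secondary objective, and the synopsis expects either nurses or oncologists to administer it. A low coefficient could mean that the two professions score differently, or only that patients moved between visits. Random change lowers the ICC and kappa. A systematic shift between visits would look like a systematic difference between professions.

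**Working it through.** **Timing.** No single sentence in the protocol dates the nurse's G8 rating. It follows from four statements:

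1. The oncologist completes G8 at the J0 consultation (synopsis, Course of the study and Summary of the study course).
2. The second rater is the nurse abbreviated IGE (section 3.3.2.2). The synopsis uses IEG for the nurse at the geriatric assessment. The nurse who handles the VES-13 at J0 is not given that abbreviation.
3. Seven G8 items come from the MNA (trial rationale), and the assessment nurse fills the MNA at the geriatric visit.
4. That visit is Step 3, J1 to J30. The Course of the study words the window differently, with an ambiguous two-week condition.

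On the J1 to J30 wording no pair is same-day. Neither wording sets a short interval for this comparison. Rater and visit are therefore aliased. The protocol plans no repeat G8 by the same rater and no same-day double rating.

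**Effect on the coefficient.** The protocol gives no target ICC, precision or sample size for the G8 comparison, so it has no figure to reproduce. Assuming equal variances and no mean shift between visits:

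observed ICC = same-day inter-rater ICC × correlation of true scores between the two visits (stability).

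Assume a same-day ICC of 0.85 (the documents give none):

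| Stability | Observed ICC |
| --- | --- |
| 1.00 | 0.85 × 1.00 = 0.85 |
| 0.95 | 0.85 × 0.95 = 0.81 |
| 0.92 | 0.85 × 0.92 = 0.78 |
| 0.80 | 0.85 × 0.80 = 0.68 |

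The value 0.92 is the one-month correlation that section 3.4.1.2 reports for the English VES-13. The other stability values are assumptions.

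**What one coefficient can identify.** An observed ICC of 0.72 fits each of these pairs of same-day ICC and stability: 0.72 × 1.00, 0.80 × 0.90, 0.90 × 0.80 and 1.00 × 0.72. Simulation with 1,000,000 pairs per setting gave ICCs of 0.7195, 0.7202, 0.7198 and 0.7203. A single all-pairs coefficient cannot tell perfect raters with changing patients from imperfect raters with stable patients.

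**Precision of a short-interval subset.** For two ratings, the approximate 95% CI width is w = √[8 z² (1 − ICC)² (1 + ICC)² / (2(n − 1))], with z = 1.96.

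- Check against the VES-13 figure in section 3.4.1.2: ICC 0.6 and n = 160 give √[8 × 3.84 × 0.16 × 2.56 / 318] = 0.199, which agrees with the stated 0.2.
- G8 subset: ICC 0.85 and n = 100 give √[8 × 3.84 × 0.0225 × 3.4225 / 198] = 0.109, about 0.11.

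**The case against.** The strongest reply has four parts.

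- *The timing is inferred.* The document is an abridged translation, section 3.3.2.2 gives no day, and the Step 3 list names the MNA but not G8. This stands as a caveat. The nurse's role and the source of the items still point to the Step 3 visit, and nothing in the text points elsewhere.

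- *Interval bands are detail for the analysis plan.* This is partly right. The protocol names the statistics without saying that all pairs must be pooled, and the missing breakdown alone would be no finding. What the protocol does fix is the design and the label: two raters on two occasions, called inter-judge, while the VES-13 comparison over the same visits is called test-retest.

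- *The loss may be small.* The only stability evidence in the document is the VES-13 correlation of 0.92 overall after one month. It already contains measurement error, so under the model above true-score stability there would be at least 0.92, and an ICC of 0.85 would fall no lower than about 0.78. It comes from a different instrument in patients over 70 on anti-androgens for prostate cancer, with subset values of 0.52, 0.60 and 0.70. It makes a mild effect plausible for G8 but does not establish one. Age, one G8 component, is effectively fixed over these weeks.

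- *Spaced ratings are a defensible choice.* Double rating at one visit risks patients repeating remembered answers, and random change makes the estimate conservative, so a high coefficient would still reassure. That is fair. A low one would remain uninterpretable.

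A reader might go further and infer that rater error and real change can never be separated in this study. The design does not support that: intervals differ between patients, so analysis by elapsed time can separate them in part. Nor do the documents show that agreement will in fact fall to 0.68, which rests on the lowest stability assumed here.

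**Conclusion.** The point holds as a limited one on a single component of a secondary objective. As written, the G8 inter-judge comparison aliases rater with occasion, and its ICC and kappa would tend to understate nurse-oncologist agreement if patients change between visits. The conclusion rests on the inferred timing of the nurse's rating. The size is unknown: from no loss to an ICC of 0.68 instead of 0.85 over the assumed range, and 0.78 at a stability of 0.92.

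A reader might infer that the validation of G8 itself is compromised. It is not on this ground: sensitivity, specificity and the sample size do not depend on this comparison.

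**What to change.** - Call the all-pairs result agreement across raters and time, and keep reporting it.
- Also report the ICC for the score, and kappa for qualitative results, by interval between J0 and the nurse's rating, for example 1–7, 8–14 and 15–30 days, or model disagreement against days elapsed.
- Rest any inter-judge statement on the shortest-interval pairs, and say that this reduces the confounding without removing it.
- State the day of the nurse's G8 rating in section 3.3.2.2, and reconcile the two statements of the geriatric visit window in the synopsis.

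No new visit or patient is needed, provided both visit dates are captured, which the protocol does not say. The cost is fewer pairs and a wider interval (about 0.11 with 100 pairs at an ICC of 0.85). The number of short-interval pairs cannot be known from the document. Patients seen quickly may also be a selected group whose score spread, and so ICC, differs, which is a further reason to keep the all-pairs figure beside the subset.

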**Assessment of the discriminating validity:**

A comparison of the score obtained to G8 and VES-13 between different groups according to the expected risk level of geriatric disorder will be performed to assess whether these questionnaires help discriminating populations for which we expect score differences (for instance, patients over 85 *vs.* patients under 85, palliative *vs.* non-palliative…).

**Assessment of the predictive validity:**

The G8 and VES-13 predictive validity will be assessed at 1 and 5 years according to the following events: mortality, disease progression, and institutionalisation.

3.3.2.3 Assessment of screening tools in various clinical situations

We will assess sensitivity, specificity, and predictive values for each screening tool, G8 and VES-13:

The type of cancer (colon, lung, ENT, breast, and lymphoma),

The therapeutic strategy (according to three groups: locoregional treatment, locoregional and adjuvant treatment, general treatment),

The stage of the disease (local, metastasis)

3.3.2.4 Assessment of geriatrics interventions

We will assess the number of interventions according to the CGA (change of initial treatment irrespective of its nature, interventions of other specialists from other fields (psychologists, psychiatrists…), nutritional intervention, kinesitherapy, and social intervention for instance), in the general population, and by type of cancer.

We will also assess each screening tool using as a reference tool the indication for geriatric intervention. We will study sensitivity, specificity, and predictive values for G8 for screening anomalies requiring a geriatric intervention.

**3.4 STATISTICAL FACTORS**

**3.4.1 Hypotheses and required number of patients**

3.4.1.1 Main analysis

For a screening tool, sensitivity and specificity are assessed jointly, although we tend to favour sensitivity as it could be damageable not to detect patients requiring a CGA. The objective then is to maximise the sensitivity of the new screening tool.

Our exploratory study suggests (Chapter 9):

a sensitivity of about 90%, when we use as gold standard the presence of an abnormal score for at least one questionnaire,

a prevalence of 50% of patients with at least one abnormal questionnaire.

Supposing that the real sensitivity for our G8 screening tool is 90%, we estimate that the inclusion of 750 patients with at least one abnormal questionnaire would be enough to estimate the sensitivity with a sufficient accuracy (2.4%) and to obtain a 95% CI between 88% and 92%. Supposing that 50% of our population will have at least one abnormal questionnaire, **1500 assessable patients** will be needed.

A patient is said to be assessable if CGA and G8 data are complete. In our exploratory study, only 309 patients out of 364 had all the necessary questionnaires for CGA (85%). In order to ensure a minimum of 1500 assessable patients, we will recruit 1650 patients.

If we want to estimate sensitivity according to the type of cancer, we will obtain an accuracy of +/- 6% for a sample of 200 patients (95% CI: 84% to 96%), and of about 5% for a sample of 400 patients (95% CI: 86% to 94%).

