| **Hypotheses and statistical analyses** | **Hypotheses and required number of patients**  The objective is to maximise the sensitivity of the new screening tool and to obtain an estimation with a satisfying accuracy. Our exploratory study suggests (section 8) a sensitivity of about 90%, when we use as gold standard the presence of an abnormal score for at least one questionnaire, and a prevalence of 50% of patients with at least one abnormal questionnaire.  The inclusion of 1500 patients would help estimating the sensitivity on a 750-patient sample with abnormal CGA, with an accuracy of 2.4% for an expected sensitivity of 90% (*i.e.* 95% CI of 87.6% to 92.4%). In order to ensure a minimum of 1500 assessable patients, we will recruit **1650 patients**.  **Statistical analyses**  The population of the study will be described broadly according to its clinical and sociodemographic characteristics in terms of size and ratio for the qualitative variables and in terms of distribution for the quantitative ones.  The following parameters will be estimated:   - The sensitivity, the specificity, and the predictive values will be estimated. 95% CIs will be reported (binomial distribution). - The ROC curve representing graphically the sensitivity according to the (1 -specificity) for various thresholds of the assessed test will be represented graphically and help determine the area under the curve (AUC). - Internal consistency will be assessed according to Cronbach’s alpha coefficient. A 95% CI will be reported. - Reproducibility will be assessed by the intraclass correlation coefficient for quantitative variables. For qualitative variables, reproducibility will be assessed by Cohen’s kappa. - Scores between acknowledged subgroups will be compared thanks to a variance analysis. - Both G8 and VES-13 questionnaires will be compared thanks to their respective area under the curve. - We will assess whether using both screening tools together (G8 and VES-13) helps obtaining a more effective screening tool compared to the sole use of one questionnaire. |

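### At the only completeness rate the protocol reports, 1650 recruits give about 1400 assessable patients, not the promised minimum of 1500; the loss of precision is small

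*Protocol*

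**What the plan says.** Protocol section 3.4.1.1 builds the main sample size in three steps.

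- Precision: with a true sensitivity of 90%, "the inclusion of 750 patients with at least one abnormal questionnaire would be enough to estimate the sensitivity with a sufficient accuracy (2.4" percentage points).
- Prevalence: "Supposing that 50% of our population will have at least one abnormal questionnaire, 1500 assessable patients will be needed".
- Incomplete data: "A patient is said to be assessable if CGA and G8 data are complete". The evidence offered on completeness is that in the exploratory study "only 309 patients out of 364 had all the necessary questionnaires for CGA (85" per cent). The conclusion follows at once: "In order to ensure a minimum of 1500 assessable patients, we will recruit 1650 patients".

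The synopsis makes the same promise in its rows on the number of patients and on hypotheses and statistical analyses: "In order to ensure a minimum of 1500 assessable patients, we will recruit" 1650. The second of these rows also gives the 1500 and 750 figures and a 95% CI of 87.6% to 92.4%. Section 3.4.1.1 rounds that interval to 88% to 92%.

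**The concern.** The recruitment target is justified by a completeness rate that does not produce it. About 15% of exploratory patients lacked a complete CGA, yet 1500 has been raised by exactly 10%. A reader who applies the quoted rate gets fewer than 1500 assessable patients, so the promise of a minimum is not supported by the evidence placed beside it.

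At stake is the enrolment figure stated in three places, and the number of abnormal-CGA patients on which the main sensitivity interval is said to rest.

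**Working it through.** **Inputs.** All are from section 3.4.1.1: 1500 assessable patients required; 1650 to be recruited; exploratory CGA completeness 309/364; prevalence of an abnormal CGA 50%; expected sensitivity 90%; 750 abnormal patients. The intervals are binomial (section 3.4.3).

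**1. The steps before the allowance for incomplete data reproduce.**
- 750 / 0.50 = 1500.
- The exact (Clopper-Pearson) 95% CI for 675/750 is 87.63% to 92.05%. Its lower arm is 90 − 87.63 = 2.37 points, which matches the stated 2.4. The normal approximation gives 1.96 × √(0.9 × 0.1 / 750) = 2.15 points.

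**2. The allowance does not reproduce.**
- Completeness: 309/364 = 0.849.
- Recruits needed for 1500 at that rate: 1500 / 0.849 = 1767 (1765 at a rounded 85%).
- The common shortcut of multiplying by 1 plus the loss also misses: 1500 × 1.15 = 1725.
- What 1650 corresponds to: 1500 × 1.10 = 1650, and 1500 / 1650 = 90.9% completeness. Neither a 10% loss nor a 91% completeness rate is stated.

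**3. Yield of 1650 at the quoted rate.**
- Assessable: 1650 × 309/364 = 1401, which is 99 (6.6%) below 1500.
- Abnormal CGA: 1401 × 0.50 ≈ 700 instead of 750.
- Allowing for sampling error in 309/364: the exact 95% CI is 80.8% to 88.4%, which gives 1333 to 1459 assessable patients. The upper end is still below 1500.

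**4. Effect on the main sensitivity estimate (90% assumed).**

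| Abnormal CGA | Exact 95% CI | Exact lower arm | Normal-approximation half-width |
|---|---|---|---|
| 750 | 87.6% to 92.1% | 2.37 points | 2.15 points |
| 700 | 87.5% to 92.1% | 2.47 points | 2.22 points |

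By the exact lower arm, which is the measure that matches the protocol's 2.4, the figure becomes 2.5. By the normal approximation it stays under 2.4.

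**5. Other precision figures.** The by-cancer intervals in section 3.4.1.1 are stated for samples of 200 and 400. The VES-13 test-retest calculation in section 3.4.1.2 rests on 160 patients, with 180 included. None of them uses the 1500.

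**The case against.** The best defence is that the protocol reports 85% as what happened before and never adopts it as the rate expected here. The exploratory cohort was regional and limited to first-line chemotherapy. This study schedules a geriatric visit with a dedicated nurse and a geriatrician, so better completeness is plausible. The document is also an abridged translation, and the chapter it cites for the exploratory study is not reproduced, so a justification may have been cut. This stands in part: a reader might infer that 1650 cannot yield 1500, and the documents do not support that. They show only that the rate 1650 requires is unstated, and that the one rate given contradicts the promise.

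A reader might also infer that requiring a complete G8 must lower the yield further. It cannot raise it, but it may leave it unchanged. The G8 as developed was seven MNA items plus age, and the MNA is part of the CGA, so in the exploratory cohort a complete CGA would largely imply a complete G8.

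Finally, one abnormal test is enough to classify a patient as abnormal, and section 3.4.2 runs the main analysis on every included patient. Some patients with incomplete assessments could therefore still count towards sensitivity, which would put the abnormal group above 700. However, section 3.4.1.1 ties the 1500 to patients with complete data, so 700 is the figure on the protocol's own definition.

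**Conclusion.** The point holds as a minor but real error in a stated sample-size guarantee. At the only completeness rate in the document, 1650 recruits give about 1400 assessable patients and about 700 with an abnormal CGA. The promised minimum of 1500 needs 90.9% completeness, for which no figure or reason is given. This rests on the exploratory 84.9% carrying over, on 50% prevalence, and on the protocol's complete-data definition of assessable.

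Two stronger conclusions are tempting. One is that the primary estimate is endangered. It is not: the lower confidence limit moves by about 0.1 point, and the protocol sets no pass or fail limit for sensitivity in its sample-size section. The other is that every precision figure in the plan falls with the 1500. Only the main sensitivity interval depends on it.

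**What to change.** Correct the text in section 3.4.1.1 and in both synopsis rows, in one of two ways.

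- **Restate the yield.** Replace the guarantee with: recruiting 1650 patients is expected to give about 1400 assessable patients at 85% completeness, of whom about 700 have an abnormal CGA. The linked text must change with it: the statement that 1500 assessable patients are needed, the 750-patient precision statement, and the two printed intervals (87.6–92.4% and 88–92%), which become about 87.5–92.1%. Changing only the guarantee would leave the plan needing 1500 while expecting 1400.
- **Keep 1500 and 750.** State the roughly 91% completeness that 1650 assumes, give the reason for expecting it when the exploratory study reached 85%, and report 1400 assessable and 700 abnormal as the yield if 85% recurs.

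Either way the cost is wording only. No further enrolment is called for, and the key dates in section 4 show inclusions closing on 08/03/2010. The first option makes the stated assessable number less favourable, with almost no change in the interval.
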